## Abstract

**Introduction:**

Secondary prevention of stroke is a leading challenge globally and only a few strategies have been tested to be effective in supporting stroke survivors. The system-integrated and technology-enabled model of care (SINEMA) intervention, a primary care-based and technology-enabled model of care, has been proven effective in strengthening the secondary prevention of stroke in rural China. The aim of this protocol is to outline the methods for the cost-effectiveness evaluation of the SINEMA intervention to better understand its potential economic benefits.

**Methods:**

The economic evaluation will be a nested study based on the SINEMA trial; a cluster-randomized controlled trial implemented in 50 villages in rural China. The effectiveness of the intervention will be estimated using quality-adjusted life years for the cost-utility analysis and reduction in systolic blood pressure for the cost-effectiveness analysis. Health resource and service use and program costs will be identified, measured, and valued at the individual level based on medication use, hospital visits, and inpatients' records. The economic evaluation will be conducted from the perspective of the healthcare system.

**Conclusion:**

The economic evaluation will be used to establish the value of the SINEMA intervention in the Chinese rural setting, which has great potential to be adapted and implemented in other resource-limited settings.

## Introduction

Stroke is one of the rising public health challenges worldwide. In 2019, there were ~12 million incident cases of stroke, of which 32.8% were in China (1). Although the stroke incidence rate is increasing, the stroke mortality rate has been decreasing over the past few decades, resulting in a huge number of stroke survivors globally (2). As these stroke survivors need continuous health management and risk control, the spending on post-stroke care causes an economic burden (3). The financial burden of stroke in rural areas is extremely severe (4, 5). As in many undeveloped areas, primary care lacks the capacity to provide guideline-based essential care to stroke patients, and community-based management for secondary prevention of stroke is far from adequate (6). Therefore, it is necessary to emphasize the prevention of recurrent strokes in the rural setting.

The system-integrated and technology-enabled model of care (SINEMA) study was designed to empower both stroke survivors and primary healthcare providers for secondary stroke prevention by training and incorporating both provider-facing and patient-facing mHealth technologies. The effectiveness of the SINEMA model has been evaluated and proven through a two-arm cluster-randomized controlled trial conducted in 50 rural villages of Hebei province in northern China (7). During the 1-year intervention, a statistically significant greater reduction in systolic blood pressure (SBP) was observed in the intervention arm compared with the control arm. Improvement in a few secondary outcomes including a 35–55% relative reduction in stroke recurrence, hospitalization, disability, and death has also been reported, which indicates the great potential benefits of the SINEMA intervention on secondary stroke prevention (8).

Despite indicating the effectiveness of the intervention, cost-effectiveness is another important factor to be considered. Previous economic evaluation studies of mHealth-based stroke prevention were reported to be cost effective. For example, the TEXT-ME trial conducted in Australia, a text message-based intervention for patients with cardiovascular diseases, reported that the intervention could gain 1,143 more QALYs and save a direct medical cost of Aus$10.56 million over a lifetime horizon for a hypothetical cohort of 50,000 patients with cardiovascular diseases in Australia (9). However, previous economic evaluations were mainly conducted in developed countries, and the cost-effectiveness of an integrated mobile health intervention on secondary stroke prevention in a resource-constrained setting like rural China remains unclear. Therefore, the economic evaluation of the SINEMA intervention is necessary. This protocol describes the methods for the economic evaluation of the SINEMA program based in a rural Chinese setting.

## Aim and objectives

This protocol describes the methods for the economic evaluation of the SINEMA program, which is nested in the SINEMA trial (8). This study aims to provide an economic evaluation of the SINEMA program to identify, measure, and value key resource and outcome impacts from the SINEMA intervention model compared with usual care for stroke secondary prevention in rural China. A within-trial economic evaluation will be conducted to calculate the within-trial incremental cost-effectiveness ratio to determine the value of the SINEMA intervention model.

## Materials and methods

### Study design

The economic evaluation is a nested study based on the SINEMA trial, a cluster-randomized controlled trial implemented in 50 villages in rural China. A detailed description of the SINEMA program and intervention design can be found in previous publications (7, 10–12). The economic evaluation will involve a within-trial cost-effectiveness analysis and cost-utility analysis with a 12-month time horizon equal to the follow-up period of the trial. We will calculate the incremental cost-effectiveness ratio in terms of the incremental cost per 1 mmHg change in systolic blood pressure, which is the primary outcome of the trial. In addition, we will also conduct a cost-utility analysis to calculate the incremental cost per quality-adjusted life year (QALY). The SINEMA intervention is deemed as cost-effective if the incremental cost per QALY is no greater than the cost-effective threshold. Following previous research (13), we will adopt the conventional approach by considering the benchmark as 1.5 times of gross domestic product per capita.

### Participants and study settings

Study participants in the economic evaluation will be the same as those recruited in the SINEMA trial. Participants were eligible if they were adults (older than 18 years), had a history of stroke diagnosed at a county or higher level hospital, were in a clinically stable condition with at least basic communication ability, and were expected to be available for the 12-month follow-up. Individuals who were unable to get out of bed had severe life-threatening diseases or had an expected life span shorter than 6 months were excluded. All participants were recruited in 50 villages from five townships in a rural county in Hebei Province, China. The county is a provincial-level impoverished county lying on the “stroke belt,” with a stroke burden double the national average level (10). Participants were recruited between 23 June 2017 and 21 July 2017 and followed until 27 July 2018.

### Intervention and control

The SINEMA intervention involved provider-side components and patient-facing components and was supported by a digital health system. In brief, village doctors, as primary healthcare providers, received training based on the train-the-trainer to train model. They were also equipped with the SINEMA app, they conducted monthly follow-up visits to patients. Additionally, financial incentives were also provided to encourage their ongoing commitment to deliver quality healthcare services. Stroke patients received monthly follow-up visits delivered by village doctors at the village clinics or their own homes if they had difficulty visiting the clinics. During each visit, they were provided with suggestions about medication use and physical activities. Participants who had access to their own or shared cell phones received one voice message, at no cost to them, for delivering health education information regarding medication adherence and physical activities.

For villages allocated to the control arm, village doctors continued their standard practices, which included practicing general clinical care and performing the “Basic Public Health Services” (BPHS). BPHS was announced when a new healthcare reform plan started in China in 2009, aiming at assisting community health organizations in delivering a set package of basic health services across the country (14). Patients in the control villages received the usual care. In the context of rural China, the usual care involved patients seeking care in village clinics, township healthcare centers, or county hospitals, as necessary. People with hypertension and diabetes may also receive quarterly follow-up visits by village doctors as covered by the Basic Public Health Services (10).

### Identification, measurement, and valuation of effectiveness

The intervention effectiveness will be measured by comparing the systolic blood pressure reduction and the QALYs between the intervention and control arm over the 12-month follow-up period.

#### Measurement of systolic blood pressure as the primary outcome

Blood pressure (BP) was measured as the primary outcome in the SINEMA trial at baseline and 1-year later, following the sample measurement protocol and approach among all participants. Blood pressure was measured on the right upper arm with participants seated and after 5 min of rest, with an electronic BP monitor (Omron HEM-7052). Two measurements were taken, and the mean value was calculated. If the difference between the two systolic BP measures was larger than 10 mmHg, a third measurement was conducted, and the mean value of the last two readings was calculated.

#### Health state utility

Health state utility (HSU) estimations will be derived from self-reported health-related quality of life (HRQoL) which was measured using the Chinese version of the EQ-5D-5L, a broadly used generic multi-attribute health utility instrument (15) at baseline and 1-year follow-up. For assessing HRQoL, study data collectors who were staff from the Center of Disease Prevention and Control in the nearby county read out the questionnaire and items for participants and collected the data. After answering the questions for EQ-5D, participants were asked to point out the health score by fingers on a paper version of the EQ-Visual Analog Scale, and then, the data collectors entered the responded values into the online survey platform. An HSU was calculated for each respondent by using the Chinese version of population-based preference weights (16), which ranged from −0.391 to 1, with 1 representing the value of full health, 0 representing deaths, and −0.391 representing the worst state.

Stroke recurrence, hospitalization, disability, and all-cause mortality were measured by using questionnaires at one-year follow-up. Medical and deaths records were also extracted from four major hospitals in the region. These data provide information about the status and trajectory of stroke during the trial period.

### Identification, measurement, and valuation of resource use and costs

The aim of the economic evaluation is to inform decision-makers about the costs and cost-effectiveness of introducing the SINEMA intervention to stroke patients in rural regions. As such, the economic evaluation will mainly be performed from the health sector perspective, reflecting the cost and values of the healthcare system.

The resources used to support the SINEMA program include as follows: (1) the cost used to support SINEMA program delivery and (2) the health resources used to support the healthcare service delivery to stroke patients. Table 1 describes the detailed measurement and valuation of costs. The research costs, including the investigator's time and data collection, were not included in the analysis. The costs of designing the SINEMA intervention and the digital health system and other “one-off” costs were excluded, but the operation and maintenance costs of the digital health system were included in the analysis.

**Table 1 T1:** Resource use information collected and measured for cost.

**Cost component**	**Measurement**	**Quantity**	**Valuation**	**potential collected resource**
**Intervention related cost**				
Part-time project manager	Time spent coordinating the project	Number of project managers	Cost of employment converted to the annual equivalent cost	Research team to record
Materials for handbooks and handouts	Inventory on printing materials	Number of materials delivered	Replacement value converted to annual equivalent cost	Research team to record
County physicians	Time spent in training village doctors and providing consultations	Number of training sessions organized	Cost of employment converted to the annual equivalent cost	Research team to record
Township manager	Time spent in coordinating and delivering consultations	Number of townships participated	Cost of employment converted to annual equivalent cost	Research team to record
Village doctors	Time spent in delivering SINEMA follow-up visits	Number of villages participated and fidelity in adhering to the intervention protocol	Cost of employment converted to annual equivalent cost	Research team to record
Voice messages	Inventory on sending voice message via third-party platform	Number of voice message delivered	Replacement value converted to annual equivalent cost	Research team to record
Maintaining the digital health system	Inventory on server cost and cost related to human resources in maintaining the program	Duration of time supporting the program	Replacement value converted to annual equivalent cost	Research team to record
Developing digital health system	Time spent in designing the program	Number of staff involved	Cost of employment converted to annual equivalent cost	Research team to record

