**Medical costs (for both intervention and control arm)**				
Inpatient cost	Time, human resources, facilities used for inpatient care	Mean days of stay and frequency of hospitalization within trial period	Mean cost replacement value recorded in social medical scheme	Reimbursement system
Outpatient cost	Time spent in delivering care	Number of follow-up visits	Replacement value converted to annual equivalent cost	(Estimated)
Medication cost	Self-reported medication use	Number of medications used and adherence rate	Replacement value converted to annual equivalent cost based on local medication price list	Follow-up survey

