#### Resources used to support program delivery

Program costs are captured based on a detailed inventory of all resources that are used to support the design and delivery of the SINEMA program. This consists of the administrative cost of headcounts of local project manager and printing materials, the cash support that compensates for the time and efforts of the village doctors, township physicians, and county physicians in delivering the SINEMA intervention over the trial period, and the resources used for maintaining the digital component of the SINEMA intervention (including daily voice messages to patients, the mobile application server, and labor cost related to system maintenance).

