#### Resources used for healthcare services

Medical costs are measured mainly by estimating the direct medical cost with individual-level data, including both inpatient costs and outpatient costs for medications. Inpatient costs during the trial period among all participants were retrospectively collected from the urban and rural resident basic medical insurance system from four major key hospitals in the region. A list of medical conditions, including cardiovascular or cerebrovascular events, or other cardiometabolic-related health conditions, is generated by researchers. All relevant inpatient records that matched the conditions will be included in the analysis and total costs will be used in the analysis. Outpatient costs were estimated by the number of hospital visits and medication use. Medication costs will be valued based on the general essential medication list and the standard unit cost for each type of medication as the “zero markups” regulation requires no additional costs on medications in the primary care settings (14).

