**Cost**		
Compensation for village doctors	Recorded headcount cost	Fidelity rate of follow-up visits ranging from lowest value to 100%
Missing information of inpatient care for those who were hospitalized in other healthcare facilities.	Median inpatient cost for same or similar diagnosis	25%, 75% percentile of inpatient cost for those who were hospitalized with same or similar diagnosis.
Missing information of outpatient cost which is not covered by health insurance.	Mean outpatient cost for same or similar diagnosis	25%, 75% percentile of outpatient cost for those who were hospitalized with same or similar diagnosis.
Missing information on medication cost of daily doses.	Mean cost for the conventional drugs	25%, 75% percentile of medication cost for those who took same or similar drugs.
Development cost of the digital health system	None	Development costs of the SINEMA model when the cost was shared by years of follow-up

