Our study design has several unique features. First, the study measures a multifaceted intervention with digital health components. Digital health interventions have a high potential to deliver interventions to a large-scale population, thus, it holds the promise of improving chronic disease management. Second, compared to human-delivered intervention, the development cost for digital health intervention is relatively high; however, the operation and marginal cost for the implementation could be limited to none if it is scaled to a large population (25). In our protocol, we followed previous studies' methods to evaluate the operational cost of the SINEMA model in our design (11). We also include the development cost in our sensitivity analysis.

As for data collection, due to the constrained funding support, the SINEMA trial observed and measured the cost and effectiveness of the intervention over a 12-month period. Although such follow-up duration was reasonable to measure a high number of stroke cases, the data collected from the trial period hardly provided information about the long-term benefits and impact of the intervention. Instead, we will use data from other trials and cohort studies that were conducted in similar settings to estimate the long-term natural transition of stroke patients in rural China (26, 27). This approach enables us to estimate the long-term economic impact of the SINEMA intervention.

The main limitation of this design lies in the field of cost measurement. First, although we measured key direct health costs at the individual level, we are only able to quantify the inpatient costs and medication costs for participants from the health insurance data. Due to the limited data access, we cannot measure the cost of inpatient care if the patients seek healthcare services beyond the major four hospitals in the study regions, which is likely to happen as there is no referral system that restricts service-seeking behaviors in rural China (27). Therefore, we tend to underestimate the inpatient costs if there are relatively more inpatients in the control group. Second, the analysis may underestimate some of the labor costs. For instance, the village doctors may provide blood pressure assessments during clinic visits for free, and the payment scheme may not be set by the number of services provided at the clinic visits. These visits were not paid, thus were not included in the financial analysis.

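### The costing rules behind the ICER numerator disagree on the price of staff time, leave the outpatient visit count open to overlap with SINEMA visits, and do not spread development cost

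*Protocol article*

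**What the plan says.** **Staff price.** In Table 1, the village-doctor row measures "Time spent in delivering SINEMA follow-up visits" and the county-physician row measures "Time spent in training village doctors and providing consultations". These two rows and the township-manager row are all valued at the cost of employment, expressed as an annual equivalent. The section on resources used to support program delivery describes the staff component as "the cash support that compensates for the time and efforts of the village doctors, township physicians, and county physicians". Table 2 takes recorded headcount cost as the base case for village-doctor compensation, and its range varies only the fidelity of follow-up visits.

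**Outpatient quantity.** The outpatient row of Table 1 applies to both arms. It measures time spent on care, takes "Number of follow-up visits" as the quantity and gives its source only as estimated. Medication has a separate row. The section on resources used for healthcare services says "Outpatient costs were estimated by the number of hospital visits and medication use". The section on intervention and control uses the term follow-up visits both for the monthly SINEMA visits and for the quarterly visits that some patients may receive under Basic Public Health Services.

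**Development cost.** Table 2 has none in the base case and, as the range, "Development costs of the SINEMA model when the cost was shared by years of follow-up". Table 1 asks for an annual equivalent cost on the same item. The study design section fixes a 12-month time horizon.

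**The concern.** The ICER is the difference in cost over the difference in effect, and the intervention is judged by comparing cost per QALY with a threshold of 1.5 times GDP per capita. The numerator therefore bears directly on the decision. Two analysts who each follow part of this text could arrive at different incremental costs.

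- Staff time is part of the intervention cost, which arises in one arm only, so a change in its price goes straight into the increment. Under the stated health-sector perspective, a payment made by the program need not equal the cost of the time used.
- If SINEMA visits also enter the outpatient row, the extra cost falls on the intervention arm alone and raises the ICER.
- If the whole development cost is charged to one year, the only analysis that tests this cost is weighted against the intervention.

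**Working it through.** The document states no unit cost, incremental cost or ICER, so there is no figure to reproduce. The check compares the rules and then illustrates how far each could move the numerator. The effect difference is held fixed and incremental cost is taken as positive. All shares, ratios, rates and useful lives below are assumptions.

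**1. Staff price.**

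| Place | Basis |
|---|---|
| Table 1 | time, at cost of employment |
| Program delivery text | cash support paid |
| Table 2 base case | recorded headcount cost |
| Table 2 range | fidelity only, so quantity and not price |

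Let w be the share of the true incremental cost due to village-doctor visits, and r the ratio of cash to employment cost. Pricing by cash multiplies the ICER by 1 − w(1 − r).

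| w | r = 0.5 | r = 0.75 |
|---|---|---|
| 0.10 | 0.95 | 0.975 |
| 0.25 | 0.875 | 0.9375 |
| 0.50 | 0.75 | 0.875 |
| 0.75 | 0.625 | 0.8125 |

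**2. Visits.** Monthly visits over 12 months give 12 per intervention participant at full fidelity, and none in control. Counted in both rows, they become 2 × 12 = 24. At an assumed 50% fidelity, 6 become 12. If both rows use the same unit price, the ICER is multiplied by 1 + w: 1.10, 1.25, 1.50 or 1.75 for w = 0.10, 0.25, 0.50 or 0.75.

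The wording allows this but does not require it. Nothing excludes SINEMA visits from the outpatient row and nothing places them there. The row could equally mean Basic Public Health Services visits, or the hospital visits named in the text. Medication has the same problem on a smaller scale: the text puts it inside outpatient cost, while Table 1 gives it its own row.

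**3. Development cost.** Let K be the total. Sharing it over one year of follow-up charges K/1 = K. The annual equivalent over a life of n years at rate i is K/A, with A = (1 − (1 + i)^−n)/i. At i = 0.03:

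- n = 3: A = (1 − 0.9151)/0.03 = 2.83
- n = 5: A = (1 − 0.8626)/0.03 = 4.58

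The one-year charge is therefore about 2.8 or 4.6 times the annuitised charge. Without discounting, the factors would be 3 and 5.

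**The case against.** **A consistent reading of the staff price exists.** The cash is described as compensating time and effort, so the recorded payment could be what the program treats as its cost of employment. That is possible, but the document does not say so. Table 1 measures time, the text counts payments, and nothing tests whether the two differ.

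**Table 1 separates intervention costs from medical costs, and the outpatient row must fit both arms.** This makes a deliberate double count unlikely. A reader might infer that the plan charges SINEMA visits twice. It does not say that, and the village-doctor quantity is villages and fidelity, not a visit count. What stands is that the outpatient quantity is defined in two ways, one of which uses the same term as the SINEMA visits.

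**Development cost is outside the base case.** This is correct, so the third part cannot move the base-case ICER. A one-year charge could serve as a conservative upper bound, but Table 2 describes it as shared, and sharing over one year shares nothing. The discussion mentions estimating longer-term impact from other studies, but it gives no number of years to divide by.

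**Three stronger readings are not supported.**

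- A reader might infer that training is both included and excluded, because one-off "costs were excluded, but the operation and maintenance costs of the digital health system were included in the analysis". No section calls training one-off, and Table 1 plainly includes it.
- The program-delivery text says its inventory covers design as well as delivery, although design is excluded elsewhere. The list that follows contains no design item, so this is a stray word and not a rule that adds cost.
- The limitation "These visits were not paid, thus were not included in the financial analysis" might be read as showing that SINEMA visits are unpriced. Its example is free blood pressure checks at clinic visits, and it is declared as a limitation.

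**Conclusion.** The point holds as an inconsistency in the costing rules that should be settled before the ICER is calculated. The staff price is worded in three ways, with no sensitivity analysis on price. The outpatient quantity differs between Table 1 and the text, which leaves a one-sided overcount possible. The development-cost rule in Table 2 does not do what it says over a 12-month horizon and does not match Table 1; this affects the sensitivity analysis only.

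Neither the size nor the net direction of any error can be fixed from the document. Cash below employment cost would lower the ICER, while counting visits twice would raise it. The multipliers depend on the assumed shares. They would be larger if savings in medical cost leave the incremental cost close to zero, since staff cost would then be a larger share of it.

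**What to change.** 1. **Staff price.** Name one basis as the base case in Table 1, the program-delivery text and Table 2, and say why it suits the health-sector perspective. Which basis to use is the sponsor's choice. Run the other as a sensitivity analysis where time records allow, and never add both. Table 1 says only that the research team is to record these items, so whether hours were logged needs to be confirmed.
2. **Outpatient row.** Define it, in both arms, as outpatient contacts other than SINEMA visits. Use the same definition in the healthcare-services text, and keep medication only in its own row.
3. **Development cost.** In Table 2, replace sharing over years of follow-up with annuitisation over a stated useful life and discount rate. It remains outside the base case.

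The cost is edits to two tables and two passages of text, plus one further sensitivity analysis. No new patient-level data are needed. The small downside is that the intervention may look somewhat more expensive if staff time is valued above the cash paid.
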